### Follow-Up

Following the home visit (6 months), participants will receive a follow-up questionnaire, including the SF-36, EQ-5D, EQ-VAS, and the CES-D to evaluate the course of their health status, quality of life, and depressive symptoms. A questionnaire asking whether and how many hypoglycemic events, visits to emergency services, and hospital admissions they experienced will also be included. In addition, participants will be asked whether they regret their participation in the study and whether they would again participate in the study. A second follow-up questionnaire with the same questions will be sent after 24 months.

After the home visit (6 months), the medical records of the participants will be examined to obtain information on the medical history, values of recent diabetes controls (HbA1c, lipids, creatinine, weight, height, blood pressure), complications (hypo- or hyperglycemic events), and visits to emergency services and hospital admissions in the year before and six months after participation in the study.

To further assess the impact of the study on participants’ treatment, GPs of participants that attended the memory clinic will receive a questionnaire 6 months after the evaluation at the memory clinic to assess whether the study led to new insights and whether it changed their treatment plan (Textbox 1).

Follow-up questions for the general practitioner (GP).Did the result come as a surprise to you or did you expect it? And why?Do you agree with the result of the memory clinic? And why?Did you adjust your diabetes treatment or management because of the results? And why?Did the results have consequences for your overall medical treatment of the patient? And why?

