For assessing the accuracy and efficiency of the diagnostic procedure (ie, the cognitive test combined with history taking; objective 3) the results of the best cognitive test and the evaluation by the GP will be combined. This should reflect the future implementation of the stepped diagnostic procedure, in which a GP will only evaluate those patients with a positive test result. Participants will be categorized in the “test positive” group when both the best cognitive test and the evaluation by the GP are positive. This combination will likely have a higher PPV than the cognitive test or the evaluation by the GP alone, leading to a more efficient diagnostic procedure. The added value of the GP’s evaluation will be assessed by calculating the adjusted ROC curve and the net reclassification index [27].

The fourth objective of this study will be addressed by comparing the difference in health status and depressive symptoms between those with and without a diagnosis of cognitive impairment, both at baseline and at the 6- and 24-month follow-up, taking into account potential baseline differences of relevant parameters. In addition, we will describe the changes that were made in diabetes care by comparing the diabetes management before and after study participation (ie, changes in treatment, number of hypo- or hyperglycemic events, emergency and hospital visits).

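### Objective 4 compares event counts from 12 months before participation with counts from 6 months after, so raw counts are expected to halve when nothing has changed

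*Protocol article*

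**What the plan says.** Two sections of the protocol article bear on this.

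- **Follow-Up** sets the source and the windows. "After the home visit (6 months), the medical records of the participants will be examined", and the items sought include "complications (hypo- or hyperglycemic events), and visits to emergency services and hospital admissions". The period covered is "visits to emergency services and hospital admissions in the year before and six months after participation in the study".
- **Statistical Analysis**, in the paragraph on objective 4, sets the comparison: "we will describe the changes that were made in diabetes care by comparing the diabetes management before and after study participation". The bracket that spells this out lists, besides treatment changes, the "number of hypo- or hyperglycemic events, emergency and hospital visits".

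Follow-Up also describes a second source of event data, the participant questionnaires at 6 and 24 months: "A questionnaire asking whether and how many hypoglycemic events, visits to emergency services, and hospital admissions they experienced will also be included". No recall period is given for them. The baseline questionnaire described under Part 1: Home Visit covers health status and depressive symptoms and does not list events.

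**The concern.** The quantity named for comparison is a number of events, and the two periods over which that number accumulates differ by a factor of two. A shorter period yields fewer events even if each patient's risk is unchanged. Read together, the two stated rules therefore build a fall into the before/after description.

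The artefact points in one direction. The Discussion presents the follow-up data, complications included, as information on the impact of the diagnostic procedure, and it says the study will inform debate on whether early recognition is desirable. An apparent drop in emergency visits, admissions or glycemic events could be read as a benefit of detection, and a real increase could go unnoticed.

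**Working it through.** The article gives no expected event rate, sample size or power for this comparison, so there is no figure of its own to reproduce.

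**Inputs**
- Before window: 12 months (Follow-Up).
- After window: 6 months (Follow-Up). Records are examined 6 months after the home visit, so the window after that visit cannot be longer.
- Measure: number of events (Statistical Analysis, objective 4).
- Group sizes, for illustration only: 513 participants, of whom 143 are planned to attend the memory clinic (Sample Size Calculation).
- Event rate r per person-year: not given. It is assumed constant over time, with a range of 0.1 to 2.0.

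**Raw counts when nothing changes**

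Expected count = r × window in years × N, so

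after/before = (r × 0.5 × N) / (r × 1.0 × N) = 0.50.

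Both r and N cancel, so the ratio rests only on the two windows and a constant rate.

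Illustration at an assumed r = 0.5:
- N = 513: 0.5 × 1.0 × 513 = 256.5 before; 0.5 × 0.5 × 513 = 128.25 after.
- N = 143: 71.5 before; 35.75 after.

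**Raw counts when the rate does change**

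Apparent ratio = true rate ratio × 0.50.
- True ratio 1.5: 0.75, so a 50% rise looks like a 25% fall.
- True ratio 2.0: 1.00, so a doubling looks like no change.

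**If the share of people with at least one event were used instead**

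Under a Poisson model the shares are 1 − exp(−r) before and 1 − exp(−r/2) after.
- r = 0.1: 9.5% and 4.9%, ratio 0.51.
- r = 0.5: 39.3% and 22.1%, ratio 0.56.
- r = 2.0: 86.5% and 63.2%, ratio 0.73.

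Exact halving is therefore a property of counts. Proportions are also distorted, by an amount that depends on the rate.

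**With counts divided by person-time**

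after/before = [(r × 0.5 × N) / (0.5 × N)] / [(r × 1.0 × N) / (1.0 × N)] = r / r = 1.00.

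**Does another source supply an equal before window?** No. The questionnaires that ask about events are described only at 6 and 24 months, so the records are the only described source of a before count.

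**The case against.** The best reply is that Follow-Up describes what is collected, while Statistical Analysis only names the variables to be described. Nowhere does the article say that undivided 12-month totals will be set against undivided 6-month totals. It is a condensed account, and a fuller protocol or analysis plan could annualise the counts, which the data allow. It stands that annualising is not ruled out. But the point does not rest on silence alone: the article states the unequal windows and states a number as the measure, and following both gives the wrong answer.

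The second reply is about weight, and it largely stands. This is a descriptive comparison within the last of four objectives. The wording of objective 4 itself names aspects of diabetes care and quality of life, and the Introduction leaves the effect on clinical outcomes to a future randomized trial. A contrast of participants with and without a diagnosis over the same window would not carry this bias.

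The third is grammatical: the window phrase could attach only to visits and admissions. The problem would then be confined to those two outcomes but would remain for them.

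A reader might go further in three ways that the article does not support:
- *That a false, statistically significant decline will be reported.* No test of these counts is planned and no event rate is given, so a probability of significance would describe an invented analysis.
- *That hypo- and hyperglycemic events are pooled into one total.* The wording does not say so, and the questionnaire asks about hypoglycemic events alone.
- *That deaths deepen the shortfall.* Death does shorten the after window, but emergency visits and admissions before death could raise the count. No mortality figure is given, and the net direction is not shown.

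**Conclusion.** The point holds for the record-based before/after event counts in objective 4. Followed as written, the plan gives an expected raw count ratio of 0.50 under no change, assuming only a constant event rate and windows of 12 and 6 months. For emergency visits and admissions the windows are explicit; for hypo- and hyperglycemic events they follow from the natural reading.

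Severity is minor to moderate. It would be tempting to say that the study's evaluation of the procedure is biased, but that goes too far: the diagnostic accuracy aims (objectives 1 to 3) and the comparison of health status and depressive symptoms between participants with and without a diagnosis do not use these counts.

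**What to change.** In the objective 4 paragraph of Statistical Analysis, state that events before and after participation are compared as rates per person-month of observation in each window, with each person's time ending at death or loss to follow-up. This uses the full year of look-back data and needs only slightly more analysis work.

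Alternatively, if event dates are extracted from the records, compare the 6 months before the home visit with the 6 months after it. Follow-Up does not say that dates are recorded, so this version may require adding them to the extraction form. It also leaves fewer before-events.

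Under either version, the report should note that the after window starts at the home visit, whereas the memory clinic diagnosis and the advice to the GP come later. Part of the after window therefore precedes any change that the advice could bring about.

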### Statistical Analysis

The diagnosis of cognitive impairment (MCI or dementia) at the memory clinic will be used as the reference standard. To address the first two objectives, participants will be classified as true positive, false positive, false negative, or true negative separately for the evaluation by the GP, TYM, and SAGE.

Not all of the patients in our study will receive the reference standard, which could lead to partial verification bias [25]. However, if only patients with the reference standard were included in the analysis (complete case analyses), the results would be biased because the selection of the patients with the reference standard will not be at random [25]. A reliable method to reduce this bias is to impute the reference standard [25]. A cognitive impairment diagnosis (yes or no) in the memory clinic will, therefore, be imputed for patients who did not attend the memory clinic. Imputed databases (N=10) will be generated with the predictors TYM, SAGE, MMSE, GP evaluation, as well as age, gender, educational level, living situation, and score on the domain mobility of the EQ-5D. The latter two are chosen because they can influence why some patients did not attend the memory clinic. With these imputed numbers, the sensitivity, specificity, positive predictive value (PPV), and negative predictive value (NPV) will be calculated.

The extent to which the cognitive tests and the evaluation by the GP discriminate between participants with and without cognitive impairment will be determined by the area under the receiver operating characteristic (ROC) curve. Next, the optimal cutoff values of the tests for this population will be determined according to the best combination of corresponding sensitivity and specificity assessed with the Youden index. The Youden index measures the effectiveness of a diagnostic marker and enables the selection of an optimal cutoff point [26]. By means of the ROC curve and the best combination of diagnostic values, the optimal instrument will be selected.

For assessing the accuracy and efficiency of the diagnostic procedure (ie, the cognitive test combined with history taking; objective 3) the results of the best cognitive test and the evaluation by the GP will be combined. This should reflect the future implementation of the stepped diagnostic procedure, in which a GP will only evaluate those patients with a positive test result. Participants will be categorized in the “test positive” group when both the best cognitive test and the evaluation by the GP are positive. This combination will likely have a higher PPV than the cognitive test or the evaluation by the GP alone, leading to a more efficient diagnostic procedure. The added value of the GP’s evaluation will be assessed by calculating the adjusted ROC curve and the net reclassification index [27].

The fourth objective of this study will be addressed by comparing the difference in health status and depressive symptoms between those with and without a diagnosis of cognitive impairment, both at baseline and at the 6- and 24-month follow-up, taking into account potential baseline differences of relevant parameters. In addition, we will describe the changes that were made in diabetes care by comparing the diabetes management before and after study participation (ie, changes in treatment, number of hypo- or hyperglycemic events, emergency and hospital visits).

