### Sample Size Calculation

For our sample size calculations, we assumed a prevalence of undiagnosed cognitive impairment of 8%. Since little quantitative information is available on the prevalence of undiagnosed cognitive impairment, we based this assumption on four considerations. The first assumption is the prevalence of dementia in the Dutch population >65 years of age is around 16% [28].The prevalence of cognitive impairment will be even higher if MCI is also considered. The second is that around half of all patients with cognitive impairment are undiagnosed. The third is the prevalence of cognitive impairment is higher in people with diabetes. And the fourth is the oldest old, in whom dementia prevalence is highest, are least likely to participate in research projects.

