In previous research in adults aged ≥59 years recruited from geriatric and memory clinics and facilities for seniors, the SAGE had a PPV of 64%, a NPV of 95%, a sensitivity of 79%, and a specificity of 95% with regard to diagnosing cognitive impairment [12]. In a memory clinic population, the TYM had a specificity of 95%, a sensitivity of 81%, a PPV of 64%, and a NPV of 98% at a cutoff score of 39 points for Alzheimer's disease. In our view, a new cognitive test should have a PPV comparable with that of the most commonly used instrument, the MMSE, which has a PPV of 53.6% for the diagnosis of dementia in primary care [29]. Therefore, for our sample size calculation, we set the lower margin for the estimated PPV at 53% (ie, 11% below the previously established PPV of 64%). With this margin and an alpha of 5% and one-sided testing (we are only interested in the lowest 5% of cognitive scores), 52 participants with a positive test result (0.11= 1.65*√(0.64*(1-0.64)/n)) are needed to have reliable, interpretable results. To achieve this number of test positive participants, given an assumed prevalence of 8% and a sensitivity of 79%, 513 participants are required. Given the test features of the TYM, this sample size should also be sufficient to determine the accuracy of the TYM. As participants will be referred to the memory clinic based on the results of all 3 tests (TYM, SAGE, and evaluation by the GP), and the results of the tests will probably not completely overlap, the group "suspected of cognitive impairment" will be larger than the group that will be tested positive on the SAGE alone. We estimate that the former group will be 50% larger than the SAGE-positive group (ie, 78 people are estimated to be in the group “suspected of cognitive impairment”). All these 78 participants will be invited to attend the memory clinic in order to establish the true and false positive rates of each of the tests. In addition, a sample (14.9%, 65/435) of the participants in which all 3 tests are negative (the screen-negatives) will be invited to the memory clinic to establish the true and false negative rates of each test. Hence, 143 participants in total will be evaluated at the memory clinic (Figure 1).

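### Cutoff and instrument are chosen in the same roughly 41 expected cases used to estimate accuracy, with no optimism correction described and the procedure's cutoff left open

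*Protocol article*

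**What the plan says.** The Statistical Analysis section of the protocol article sets out a chain of steps, all in the study's own participants:

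- The missing memory clinic diagnoses are imputed (10 datasets). Participants are classified against the reference standard separately for TYM, SAGE and the GP evaluation, and sensitivity, specificity, PPV and NPV are calculated.
- ROC areas follow, and then the Youden step: "the optimal cutoff values of the tests for this population will be determined according to the best combination of corresponding sensitivity and specificity".
- The test is chosen: "By means of the ROC curve and the best combination of diagnostic values, the optimal instrument will be selected".
- For objective 3, "the results of the best cognitive test and the evaluation by the GP will be combined". The procedure is positive only when both components are positive. The GP's added value is judged by an adjusted ROC curve and the net reclassification index.

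Fixed cutoffs also exist. Under Screening Tests and in Part 2 (Selection Criteria for Memory Clinic Visit) they are TYM ≤39 and SAGE ≤14, and they decide referral. The GP evaluation is a binary judgement with no derived cutoff.

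**The concern.** Taking the highest Youden index over all cutoffs, and then the better of two tests, keeps whatever sampling noise happened to favour the winner. If the winner's accuracy is read off in the same participants, it is biased upward. The bias falls where data are scarcest, in the cases, and therefore on sensitivity, which tells a GP how many impaired patients the procedure misses. The Discussion presents the procedure as ready for daily practice and as the basis for advice to GPs.

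A second gap adds to this. The text never says which cutoff enters the combined procedure, so a reader cannot tell whether its reported accuracy will be prespecified or data-derived.

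**Working it through.** **Inputs from the Sample Size Calculation section.** Prevalence: "we assumed a prevalence of undiagnosed cognitive impairment of 8"%. Size: "given an assumed prevalence of 8% and a sensitivity of 79%, 513 participants are required". Published accuracy: "the SAGE had a PPV of 64%, a NPV of 95%, a sensitivity of 79%, and a specificity of 95"%, and "the TYM had a specificity of 95%, a sensitivity of 81"%. Precision: "an alpha of 5% and one-sided testing", with an 11-point margin on a PPV of 64%.

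**The plan's own figures.** Test positives: 1.65² x 0.64 x 0.36 / 0.11² = 51.84, rounded up to 52, as printed. Total: 52 x 0.79 / 0.08 = 513.5, which matches the printed 513. The usual route through the PPV gives 52 x 0.64 / (0.79 x 0.08) = 526.6. The 3% difference does not matter here.

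**Expected cases.** 513 x 0.08 = 41.04, leaving about 472 non-cases. These are cases after imputation, since 143 of 513 (28%) are to be verified.

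**Discrimination implied by the published figures.** With normal scores, the separation is z(0.79) + z(0.95) = 0.806 + 1.645 = 2.451 for SAGE and 0.878 + 1.645 = 2.523 for TYM. AUC = Φ(separation/√2), about 0.96 for both. The SAGE figures come from geriatric and memory clinics and facilities for seniors. The TYM figures come from a memory clinic population and concern Alzheimer's disease. Lower values are therefore plausible for undiagnosed MCI or dementia in primary care.

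**Simulation.** Each run draws 41 cases and 472 non-cases with two correlated normal scores. Scores are grouped in steps of 0.2 to 0.5 SD because TYM (0 to 50) and SAGE (0 to 22) are integer scales. Each test gets its Youden cutoff and the better test is kept. Optimism is apparent minus true sensitivity at the chosen cutoff. The correlations, the GP's sensitivity and the score steps are assumptions, not figures from the documents. Every participant is treated as verified.

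Central setting (test correlation 0.5, GP sensitivity 80%, GP-test correlation 0.3, test picked by Youden index):

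| AUC | Apparent sensitivity, selected test | True | Optimism, test | Optimism, procedure | Specificity optimism, test |
|---|---|---|---|---|---|
| 0.96 | 92.1% | 88.0% | 4.1 | 2.7 | 0.4 |
| 0.90 | 85.2% | 80.2% | 5.0 | 3.6 | 0.4 |
| 0.80 | 76.6% | 70.5% | 6.1 | 4.3 | 0.5 |

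Varying the test correlation (0.3, 0.7), GP sensitivity (60%, 80%, 95%) and the score steps:

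- AUC 0.96: 3.3 to 4.5 points for the test, 1.4 to 3.9 for the procedure.
- AUC 0.80: 5.0 to 6.6 points for the test, 2.8 to 6.0 for the procedure.

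**Fixed cutoffs, choosing only the test.** At the published sensitivities and specificities, optimism is 2.5 to 3.0 points for the test and 1.9 to 2.2 for the procedure.

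**Number of cases.** At AUC 0.96 and GP sensitivity 80%, 25 cases give 5.6 points (test) and 4.1 (procedure); 100 cases give 1.9 and 1.2. This matters because the interim check after 80 inclusions may change the sample size.

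**Net reclassification.** For two binary rules the index equals the Youden index of test-and-GP minus that of the test alone. In the table the sensitivity part of its bias is 2.7 - 4.1 = -1.4 points at AUC 0.96 and 4.3 - 6.1 = -1.8 at AUC 0.80. With the specificity part included (assumed GP specificity 90%), the bias was -1.2 to -3.5 points in nine settings (AUC 0.80 to 0.96, GP sensitivity 60% to 90%). The sign is negative because selection inflates the test alone more than the combination.

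**Scale.** The standard error of a 79% sensitivity on 41 cases is √(0.79 x 0.21 / 41) = 6.4 points.

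**The case against.** The strongest reply is that the plan already holds much of the safeguard. Fixed cutoffs are stated, and the first calculation of sensitivity and specificity comes before the cutoff search, so the natural reading is that accuracy at ≤39 and ≤14 is reported first. If the procedure also uses those cutoffs, only a choice between two tests remains, worth about 2 points. This stands as a limit on size. It does not settle the matter, because the text does not say which cutoff the procedure uses or which estimate is primary.

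Second, this is a condensed article, and internal validation could be specified in a fuller plan. That also stands: one can say only that no correction is described here, not that none exists. The chain of selection, however, is set out step by step, and following it as written produces the bias.

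Third, the bias is below one standard error of sensitivity in most settings. That is true, but it is systematic, and an uncorrected interval would be centred too high.

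Three stronger readings are tempting and lack support:

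- A reader might infer that the procedure's sensitivity will be overstated by about 5 points. That size suits the selected test. The GP requirement dilutes it, to about 3 points at the published accuracy with GP sensitivity 80%. About 5 points needs a weaker test, mostly together with a very sensitive GP evaluation.
- A reader might infer that net reclassification would look too good. For binary rules the bias runs the other way.
- A reader might infer that partial verification must enlarge the bias. The main calculation does not model imputation. A run with inverse-probability weights as a stand-in gave larger values (for example 4.3 rising to 5.1 points), but that is not the planned method.

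**Conclusion.** The point holds in limited form. Cutoffs and instrument are selected in the same roughly 41 expected cases that yield the accuracy estimates. No optimism correction is described, and the cutoff for the combined procedure is unspecified.

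Sensitivity is overstated by about 3 to 7 points for the selected test at its derived cutoff and by about 1.5 to 6 points for the test-and-GP procedure. If the fixed cutoffs are kept and only the test is chosen, the procedure's figure is about 2 points. Specificity is hardly affected. The GP's added value by net reclassification would be slightly understated.

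The direction follows from the stated rules. The size rests on 8% prevalence, integer-like normal scores, AUC 0.80 to 0.96, test correlation around 0.5 (0.3 to 0.7 tried) and GP sensitivity of 60% to 95%. The form of the net reclassification index is not stated, so its sign is shown only for the two-category version. The matter should be dealt with before analysis, but it does not undermine the design.

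**What to change.** - State that accuracy at the prespecified cutoffs (TYM ≤39, SAGE ≤14) is the primary estimate for each test, and that Youden-derived cutoffs are secondary.
- State which cutoff enters the combined procedure.
- For the selected test and the procedure, report optimism-corrected sensitivity, specificity, PPV and NPV from a bootstrap that repeats imputation, cutoff search and choice of test in every resample. Apply the same correction to the net reclassification index.
- Report the paired TYM-SAGE difference with its interval, so that the reader can see how firmly the data favour one test.

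The cost is analysis programming and slightly less favourable reported accuracy. No new data or extra participants are needed.

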### Objectives

Our overall aim is to establish a reliable, valid, and efficient stepped diagnostic procedure to detect undiagnosed cognitive impairment in patients ≥70 years of age with type 2 diabetes. The procedure will consist of a self-administered cognitive test and an evaluation by a GP. Additionally, we will describe how early detection of cognitive impairment affects treatment and quality of life in participating patients in a parallel observational study. The specific objectives of the study are (1) to assess the validity of two self-administered cognitive tests (TYM and SAGE) in detecting undiagnosed cognitive impairment in elderly patients with type 2 diabetes in a primary care setting and to select the best instrument, (2) to assess the diagnostic accuracy of a standardized evaluation by a GP in detecting undiagnosed cognitive impairment in patients with type 2 diabetes, (3) to estimate the accuracy and efficiency of the best cognitive test(s) combined with the evaluation by the GP, and (4) to describe the effect of the diagnostic procedure on several aspects of diabetes care (ie, treatment targets and appointment schedules) and patients’ quality of life.

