#### Part 2: Selection Criteria for Memory Clinic Visit

After the home visit, an independent physician, not involved in the home visit or in the memory clinic, will determine whether the participant will be selected for a visit to the memory clinic of the University Medical Centre Utrecht. To minimize the influence of the increasing experience of the research physician because of the growing number of home visits during the study period, the research physician who visited the participant at home will not be informed about the results of the memory clinic. The following 3 criteria will be used to decide whether a participant will be invited to the memory clinic (1) a classification of “suspected of cognitive impairment” by the research physician, (2) a score of ≤39 on the TYM, and (3) a score of ≤14 on the SAGE. When a participant scores positive on one of these criteria, the participant will be invited to the memory clinic. In addition, a random sample of 15% (65/435) of participants with negative scores on all 3 criteria will be invited to the memory clinic (see sample calculation below and Figure 1).

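### Objective 4 is worded as an effect of the diagnostic procedure, but its quality-of-life contrast compares people by disease status and can only describe course by diagnosis

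*Protocol article*

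**What the plan says.** The Objectives section of the Protocol article gives the fourth aim as "to describe the effect of the diagnostic procedure on several aspects of diabetes care" and on quality of life. The same section says "we will describe how early detection of cognitive impairment affects treatment and quality of life in participating patients in a parallel observational study".

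The Statistical Analysis section addresses this aim in two ways. For health status and depressive symptoms it plans "comparing the difference in health status and depressive symptoms between those with and without a diagnosis of cognitive impairment", at baseline, 6 and 24 months, "taking into account potential baseline differences of relevant parameters". For diabetes care it plans "comparing the diabetes management before and after study participation", with no control group. The Follow-Up section adds a questionnaire to the GPs of clinic attenders.

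On who reaches the clinic, the Sample Size Calculation says of the suspected group: "All these 78 participants will be invited to attend the memory clinic". Of the rest, Part 2 (Selection Criteria for Memory Clinic Visit) says "a random sample of 15% (65/435) of participants with negative scores on all 3 criteria will be invited to the memory clinic". The stated purpose of that sample is diagnostic accuracy: these people "will be invited to the memory clinic to establish the true and false negative rates of each test". The SF-36, EQ-5D, EQ-VAS and CES-D are collected at the home visit and again 6 and 24 months later. The Follow-Up section does not restrict these questionnaires to clinic attenders.

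**The concern.** The objective asks what the procedure, or detection, does to people. The contrast asks how people with impairment differ from people without it. To separate the two, one would need impaired people who went undetected, and by design there is no such group: all participants are screened and all screen-positives are invited.

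A person with a clinic diagnosis therefore differs from one without it both in having the disease and in having been told of it. Adjusting for baseline makes the groups comparable at the start. It does not make their later course the same, and a steeper decline is what one would expect of cognitive impairment.

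At stake is what may be concluded. The Discussion asks whether informing patients harms or helps their mood and quality of life, and promises observational information on the impact of such procedures. A worse course in the diagnosed group could be taken as harm from diagnosis, or a benefit could be hidden by disease decline.

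**Working it through.** **Group sizes.** The plan gives no sample size or power for objective 4, so the sizes come from the accuracy calculation.
- Test positives: 0.64 × 0.36 × (1.65/0.11)² = 51.84, rounded up to 52, as stated.
- Suspected: 52 × 1.5 = 78.
- Screen-negatives, taking the stated total of 513: 513 − 78 = 435.
- Invited at random: 65/435 = 14.9%. Not invited: 435 − 65 = 370.
- Clinic total: 78 + 65 = 143.

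The plan's group sizes reproduce.

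**How far disease course alone can drive the planned contrast.** Assume detection has no effect, and that 34 of the 143 are diagnosed and 109 are not. The 34 is illustrative: 513 × 0.08 = 41.0 impaired; 0.79 × 41.0 = 32.4 detected; plus about 1.3 found among the 65 (derived below), or 33.7.
- SE = √(1/34 + 1/109) = 0.196 SD.
- Chance of a significant difference at two-sided 5% = Φ(g/SE − 1.96), where g is the extra decline due to disease. With baseline adjustment, SE is multiplied by √(1 − ρ²), where ρ is the baseline to follow-up correlation.

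| Assumed g | Unadjusted | ρ = 0.5 | ρ = 0.7 |
|---|---|---|---|
| 0.3 SD | 33% | 42% | 57% |
| 0.5 SD | 72% | 84% | 95% |

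Adjustment leaves g in the estimate and narrows the interval around it, so a difference due to disease course alone becomes more likely to reach significance. The documents give no value for g, ρ or the number diagnosed; all are assumptions.

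**What the random invitation could show.** Compare 65 invited with 370 not invited.
- SE = √(1/65 + 1/370) = 0.134 SD.
- 95% half-width = 1.96 × 0.134 = 0.26 SD. At an assumed correlation of 0.6 this is multiplied by √(1 − 0.36) = 0.8, giving 0.21 SD.
- Detectable difference at 80% power, two-sided 5%, unadjusted: (1.96 + 0.842) × 0.134 = 0.38 SD. At assumed response rates of 80% and 60% it is 0.42 SD and 0.49 SD.
- Power with full follow-up, unadjusted: 32% at 0.2 SD, 61% at 0.3 SD and 84% at 0.4 SD.

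**What it could not show.** On the plan's inputs, 41.0 people are impaired. If the SAGE alone misses 21%, the three criteria together miss at most 41.0 × 0.21 = 8.6 people, or 8.6/435 = 2.0% of screen-negatives. That is about 65 × 0.020 = 1.3 people among the invited, and 0.3 to 0.6 if only 5% to 10% are missed (assumed). If detection affects only the impaired, a true effect of 0.5 to 1.0 SD is diluted to 0.010 to 0.020 SD. The power to find it is about 3%, hardly above the 2.5% expected in that direction with no effect.

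**The case against.** The strongest defence is that the plan does not claim a causal result. It says this part will describe, calls it observational, adjusts for baseline and leaves the effect on clinical outcomes to a later randomised trial. That stands. A reader might infer that the authors intend to read the effect of the disease as the effect of detection; nothing in the Statistical Analysis section says so. What remains is that the Objectives and Discussion use the language of effect and impact for quality of life, which this contrast cannot support.

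The contrast also has a proper use. At baseline, before anyone is told, it bears on the Discussion's other idea, that undiagnosed impairment may itself lower quality of life. And the diabetes-care half of objective 4 rests on the before-after description and the GP questionnaire, so the point does not extend to it.

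Three further readings go too far:
- **The random invitation answers the Discussion's question.** It does not. Almost nobody among the screen-negatives would be told of an impairment, and the intended stepped procedure would not send screen-negatives on to a GP evaluation.
- **Comparing diagnosed with undiagnosed people within the suspected group removes the problem.** It equalises the work-up, but disease status still differs between the groups.
- **The group without a diagnosis pools verified normals with about 370 unexamined people.** The article does not say this. It could equally mean attenders only, or the imputed status used for the accuracy analyses. A condensed article may leave that detail to the full protocol.

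**Conclusion.** The mismatch is real but bounded. The planned contrast can describe how health status and mood run in people with and without a diagnosis; it cannot estimate what the procedure or detection does to them. Any difference in disease course passes one for one into the estimate. The rejection rates shown are illustrations under assumed declines, correlations and numbers diagnosed.

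The unused randomised comparison is worth having but narrow. It is precise to about ±0.26 SD with full follow-up for the effect of a clinic invitation in screen-negatives, and it does not cure the confounding in the main contrast. The expected one impaired person among the 65 rests on the plan's assumed 8% prevalence and the 79% sensitivity it cites. The accuracy objectives, 1 to 3, are untouched.

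**What to change.** 1. Restate the comparison of health status and depressive symptoms as a description of course by diagnosis. Drop the wording of effect or impact of the procedure, or of detection, for these outcomes in the Objectives and Discussion. Define the groups by the diagnosis actually made at the clinic, not by imputed status, because people with an imputed diagnosis were never told of one.
2. Add a limited secondary analysis among screen-negatives: the 65 randomly invited against the 370 not invited, analysed by invitation whether or not the person attended. Compare SF-36, EQ-5D, EQ-VAS and CES-D at 6 and 24 months with baseline adjustment, and report differences with 95% intervals. State beforehand that it concerns the burden or reassurance of a memory-clinic work-up in screen-negatives only.

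The cost is wording and one extra analysis, with no new visits or data. The downside is a narrower claim for objective 4, and a secondary result that says nothing about disclosing impairment and loses precision with non-response.
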